## Abstract

**Background:**

Adjunct treatment with a popliteal plexus block (PPB) provides moderate enhancement to multimodal analgesic regimens following total knee arthroplasty while maintaining motor function. However, the optimal anesthetic volume of local anesthetic for PPB remains unknown.

**Aim:**

To compare the analgesic effects of PPB with 10 versus 20 mL of local anesthetics as an adjunct to a femoral triangle block after total knee arthroplasty.

**Methods:**

This blinded, controlled, randomized clinical trial will include 120 patients, randomly assigned to receive PPB with either 10 or 20 mL of bupivacaine 5 mg/mL. All patients undergo primary total knee arthroplasty under spinal anesthesia and receive a multimodal analgesia regimen, including paracetamol, ibuprofen, opioids, dexamethasone, and a femoral triangle block.

**Outcomes:**

Primary outcome is 24‐h postoperative opioid consumption. Secondary outcomes include the frequency of patients with opioid‐free analgesia in the first 24 h after surgery, postoperative pain intensity at rest and during mobilization, postoperative muscle function of the leg, ability to mobilize with crutches 6 h after surgery, and Quality of Recovery‐15 survey at 24 h after surgery.

**Conclusion:**

This trial hopes to optimize postoperative pain management after total knee arthroplasty by providing valuable insights into the optimal analgesic volume for PPB.

**Trial Registration:** Danish Data Protection Agency: 693807, clinicaltrials.gov: NCT06908837, CTIS: 2024‐520204‐26‐00

AbbreviationsmLmillilitersMMEmorphine milligram equivalentsPPBpopliteal plexus blockREDCapResearch Electronic Data Capture softwareTKAtotal knee arthroplasty

## Introduction

1

Primary total knee arthroplasty (TKA) is often associated with severe postoperative pain, highlighting the importance of multimodal analgesia in pain management. Mul helps reduce pain and opioid use, prevent complications, and enhance patient satisfaction [1, 2]. Peripheral nerve blocks are recommended for this multimodal analgesia [3, 4].

The popliteal plexus block (PPB) is a newer peripheral nerve block technique used to enhance multimodal analgesia following TKA. The PPB targets sensory genicular nerves in the popliteal fossa which innervate the posterior aspects and intra‐articular structures of the knee. The PPB complements peripheral nerve blocks for the antero‐medial aspects of the knee, such as the adductor canal block or femoral triangle block. Clinical trials have demonstrated that adjunct treatment with PPB can reduce pain scores and postoperative opioid consumption after TKA without impairing the motor function of the leg [5, 6, 7, 8]. Sørensen et al. [5, 8] reported a 24‐h opioid reduction after TKA equivalent to 15–25 mg of oral morphine with the use of 10 mL of local anesthetic for PPB, whereas Jiang et al. observed a reduction equivalent to 45 mg with 20 mL. Notably, neither study reported significant motor impairment. This motor‐sparing efficacy of the PPB was recently confirmed in a study evaluating the motor effects of 10, 20, and 30 mL of local anesthetic in healthy volunteers [9]. Collectively, these findings suggest a favorable analgesic profile for PPB using larger volumes of local anesthetic without compromising motor function. As the optimal analgesic volume for PPB remains unknown, further randomized clinical trials are necessary.

This trial aims to assess the analgesic effect of PPB with 10 versus 20 mL of local anesthetic as an adjunct to femoral triangle block in a multimodal analgesic regimen following primary unilateral TKA. We hypothesize that PPB with 20 mL of local anesthetic reduces 24‐h postoperative opioid consumption compared with 10 mL after TKA.

## Methods

2

### Trial Design, Randomization, Monitoring, and Approvals

2.1

This single‐center, blinded, controlled, randomized clinical trial will be conducted at Silkeborg Regional Hospital, Denmark. The trial follows a parallel design (Figure 1), with one group receiving a PPB with 10 mL of bupivacaine 5 mg/mL and the other group receiving a PPB with 20 mL of bupivacaine 5 mg/mL, in addition to multimodal analgesia following TKA. A total of 120 patients will be included and allocated in a 1:1 ratio using computer‐generated block randomization (blocks of 10), managed by an independent data manager in REDCap. The trial will be monitored by the Good Clinical Practice Unit at Aarhus University Hospitals, conducted according to the Declaration of Helsinki and presented in adherence to the Consolidated Standards of Reporting Trials statement [10]. The trial is approved by the Medical Research Ethics Committees and the Danish Medicines Agency (CTIS‐number: 2024‐520204‐26‐00) and registered at the Danish Data Protection Agency and at clinicaltrials.gov (NCT06908837).

**FIGURE 1 aas70057-fig-0001:**
[figure not shown]
Flow diagram of enrolment. Abbreviations: ASA, American Society of Anaesthesiologists physical status classification; BMI, body mass index; *n*, number of patients; PPB, popliteal plexus block.

### Inclusion and Exclusion Criteria

2.2

Patients eligible for inclusion are adults over 18 years scheduled for primary TKA under spinal anesthesia, able to provide written informed consent, and classified as American Society of Anaesthesiologists physical status 1, 2, or 3. Exclusion criteria are inability to read or speak Danish, lack of access to a smartphone with internet, allergies to study medications, preoperative consistent daily opioid intake, reliance on walking aids, substance abuse, BMI over 40, or a diagnosis of neurodegenerative disorders.

### Blinding

2.3

Anesthesiologists performing the peripheral nerve blocks are not blinded to treatment allocation; consequently, they are excluded from data collection and analysis.

All patients, outcome assessors, data analysts, and other personnel involved in the treatment of the patient will be blinded. Patients are shielded from observing their legs and the ultrasound monitor during the nerve block procedure by an opaque cloth hanging at chest level. Furthermore, patients are unlikely to sense the nerve block procedure, as it is performed postoperatively, whereas the effect of spinal anesthesia persists. Even after the spinal anesthesia wears off, patients are likely unable to distinguish between the injection of 10 and 20 mL of bupivacaine for the PPB. The independent data manager blinds group status, dates, and patient‐identifiable data before sending the dataset to the blinded principal investigator, who will perform the statistical analysis. Conclusions on all outcome analyses will be completed with blinding intact before unblinding the dataset.

### Outcomes

2.4

The primary outcome is total opioid consumption from *T*
_0_ (end‐of‐surgery time) to *T*
_24_ (24 h after *T*
_0_), expressed in oral morphine milligram equivalents (MME).

Secondary outcomes include:
The frequency of patients with opioid‐free analgesia from *T*
_0_ to *T*
_24_.Pain at rest at *T*
_6_ (6 ± 1 h after *T*
_0_) and at *T*
_24_.Pain during a 10‐m walk with crutches at *T*
_6_ and *T*
_24_.The frequency of patients unable to walk 10 m with crutches at *T*
_6_.The frequency of manual muscle test (MMT) < Grade 3 for dorsiflexion and plantarflexion of the ankle and knee extension at *T*
_6_.Patient‐reported quality of recovery (Quality of Recovery‐15) at *T*
_24_.

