### Study Period, Data Collection, and Analyses

2.8

The study period begins on the day of surgery, after signing the informed consent form prior to the surgery. The study period ends 24 h after the end‐of‐surgery time (=*T*
_24_). The length of the patient's hospitalization during the study period is determined by their agreement with the surgeon. Patients are allowed to be discharged during the study period.

Pain intensity will be assessed using the 11‐point Numeric Rating Scale (NRS) ranging from 0 = *no pain* to 10 = *worst imaginable pain*. Preoperative baseline pain intensity at rest and during a 10‐m walk will be obtained on the day of surgery.

Prior to assessment of postoperative walking ability with crutches, muscle function is evaluated using the MMT for dorsiflexion and plantarflexion of the ankle, as well as knee extension. MMT results will be graded from 5 to 0 [13]:

5 = active motion against gravity with maximum resistance from assessor.

4 = active motion against gravity with moderate resistance from assessor.

3 = active motion against gravity without resistance.

2 = active motion with gravity eliminated or minimal assistance from assessor.

1 = no active motion, but palpable or observable muscle contraction.

0 = no active motion or muscle contraction.

At *T*
_24_, patients will be sent an automated text message including a survey link. In the survey, patients will report their intake of the dispensed morphine tablets, pain intensity at rest and during a 10‐m walk with crutches, and complete the Quality of Recovery‐15 questionnaire [14]. Total opioid consumption will be reported as oral MME, combining hospital‐administered opioid doses from the patient file and self‐reported intake of dispensed morphine tablets.

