Total opioid consumption and Quality of Recovery‐15 will be assessed with histograms and Q–Q plots and analyzed using *t*‐tests or Mann–Whitney *U* tests. Pain intensity will be analyzed with repeated measures ANOVA or linear mixed‐effects models. Differences in frequencies will be analyzed using chi‐squared or Fisher's exact tests, as appropriate. An alpha level of 0.05 is used to determine statistical significance. We predefine the minimal clinically relevant difference between the groups in the total opioid consumption as 15 mg of oral MME [15]. Analyses will follow the intention‐to‐treat principle. Missing data will not be imputed or included in the analyses, but the frequency and reasons will be reported in the article. Any changes to the statistical plan will be reported, with the final detailed plan included in the publication.

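### Walking pain at T6 is compared only among patients able to walk, because the no-imputation rule removes the rest; this secondary comparison is biased if inability is pain-related and differs between groups

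*Protocol article*

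**What the plan says.** Section 2.4 of the protocol article lists two secondary outcomes that depend on the same T6 walk. One is "Pain during a 10‐m walk with crutches at" T6 and T24. The other is "The frequency of patients unable to walk 10 m with crutches at" T6. The plan therefore expects that some patients will not complete the walk.

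Section 2.8 sets the handling:

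- Scale: "Pain intensity will be assessed using the 11‐point Numeric Rating Scale (NRS"), from 0 to 10. No value or rule is given for a patient who cannot walk.
- Model: "Pain intensity will be analyzed with repeated measures ANOVA or linear mixed‐effects models". The choice between the two is left open.
- Missing values: "Missing data will not be imputed or included in the analyses, but the frequency and reasons will be reported in the article".
- Population: "Analyses will follow the intention‐to‐treat principle".
- Inability to walk is tested on its own: "Differences in frequencies will be analyzed using chi‐squared or Fisher's exact tests, as appropriate".

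**The concern.** Inability to walk at six hours is a result that pain or leg weakness can produce, and the volume of local anesthetic could plausibly affect either. The plan treats it as a result in section 2.4. Under the general rule in section 2.8, the same event acts as a missing value in the walking-pain analysis. Followed as written, the plan compares T6 walking pain among patients selected after randomization.

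If pain stops more patients from walking in one group than in the other, the group with more non-walkers loses more of its high scores and looks better than it should. A real benefit of 20 mL could be understated. With the rates reversed, it could be overstated. What is at stake is one time point of one secondary outcome, and possibly its T24 value as well, depending on the model chosen.

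**Working it through.** **The plan's own figure.** The article states no figure for walking pain or for the share unable to walk. Its only calculated figure is the sample size for opioid consumption. With SD 31.8, difference 15, one-sided α = 0.05 and power 0.80, n = 2 × (31.8/15)² × (1.645 + 0.842)² = 55.6. This rounds up to the stated 56 per group but does not bear on this point.

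**Assumed inputs.** All of the following are assumptions.

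- Walking pain has SD 2.5 NRS points, around a mean of 5 with 10 mL.
- A latent tendency to be unable to walk has correlation ρ with walking pain, from 0 to 0.8.
- Between 5% and 30% of a group are unable to walk.

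**Size at T6.** If a fraction r cannot walk, the mean among walkers falls below the mean of the whole group by ρ × SD × k(r). Here k(r) = φ(z)/(1 − r), where z is the normal quantile at 1 − r.

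- k(0.05) = 0.1031/0.95 = 0.109
- k(0.10) = 0.1755/0.90 = 0.195
- k(0.20) = 0.2800/0.80 = 0.350
- k(0.30) = 0.3477/0.70 = 0.497

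The bias in the difference (20 mL minus 10 mL) is ρ × 2.5 × [k(r at 10 mL) − k(r at 20 mL)]. The simulation column rounds scores and limits them to 0–10, with 1,000,000 patients per group.

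| Unable, 10 mL vs 20 mL | Formula, ρ = 0.3 | Formula, ρ = 0.8 | Simulation, ρ = 0.3 to 0.8 |
|---|---|---|---|
| equal rates | 0 | 0 | about 0 |
| 10% vs 5% | 0.06 | 0.17 | 0.06 to 0.17 |
| 20% vs 10% | 0.12 | 0.31 | 0.11 to 0.30 |
| 30% vs 10% | 0.23 | 0.60 | 0.21 to 0.60 |
| 10% vs 20% | −0.12 | −0.31 | −0.11 to −0.30 |

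With ρ = 0 every row is 0. The simulated bias is about the same whether the true difference is 0 or about −1.

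**Extreme case.** Suppose pain alone decides, with a hard cut-off, means 5 and 4, and SD 2.2. Removing every score of 8 or more (8.6% vs 3.5% unable) leaves means of 4.62 and 3.83, so a true difference of 1.0 becomes 0.80. With the cut-off at 7 (18% vs 9%), the means are 4.29 and 3.62, and the difference is 0.67.

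**Effect of the model choice.** Take no true difference, 20% vs 10% unable, ρ = 0.8, and a correlation of 0.5 between T6 and T24 pain.

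- Complete-case repeated measures ANOVA: a spurious difference of 0.31 at T6 and 0.5 × 0.31 = 0.155 at T24, because the whole patient is lost.
- Mixed model: T24 scores are kept, so the T24 bias is about 0. At T6 the retained T24 scores correct part of the bias. With a slope of T6 on T24 of about 0.41 among walkers, 0.31 − 0.41 × 0.155 = 0.25 remains.

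A single simulation with 8,000 patients per group gave 0.37 and 0.21 for complete cases, and 0.28 and 0.04 for the mixed model. Its standard error is about 0.04, so it agrees with these values within chance.

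**Would the separate test give warning?** For 12/60 vs 6/60 unable, the uncorrected chi-squared is 120 × (12 × 54 − 6 × 48)² / (60 × 60 × 18 × 102) = 2.35, p = 0.13. A twofold imbalance can pass as non-significant.

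**The case against.** The strongest reply is that the plan already reports ability to walk beside pain among walkers, and that this pair is interpretable. It also promises the frequency and reasons of missing data, and a final detailed plan with the publication. This stands in part. Separate reporting makes the selection visible, but it does not correct the pain comparison. The general missing-data rule is stated in the article, so the point is not simply detail left to a later document.

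Four stronger readings are tempting, and the documents do not support them.

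- *Harm from weakness would be hidden.* It would not. Inability to walk and manual muscle test below Grade 3 are both listed secondary outcomes with their own tests.
- *The plan contradicts its intention-to-treat statement.* This goes too far. The exclusion of missing values is disclosed, and patients unable to walk stay in their allocated group and can contribute to all other outcomes, including the primary one. The tension concerns incomplete data in one outcome.
- *Non-walkers lose their T24 score.* This follows only under complete-case repeated measures ANOVA. The plan equally allows a mixed model, which keeps that score.
- *Those excluded are the patients in most pain.* This is plausible but not shown. Inability may come from motor block or dizziness, and the introduction cites no significant motor impairment in earlier trials of the block. That non-walkers have no score is itself an inference, because the article does not say how a patient who tries and stops is scored.

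An objection to the remedy also has force. Giving every non-walker the worst score in the main analysis would count a painless motor block as maximal pain. That argues for a sensitivity analysis and against replacing the main one.

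**Conclusion.** The concern holds for a secondary outcome. As written, the plan compares T6 walking pain conditional on being able to walk. Under the assumed inputs the bias is zero when inability is unrelated to pain and about zero when rates are equal under the same mechanism in both groups. Otherwise it is about 0.06 to 0.60 NRS points, favoring the group with more non-walkers. The hard cut-off case (a loss of 0.20 to 0.33 from a true 1.0) shows what happens if pain alone decides and should not be read as the expected size. The article gives neither the share unable to walk nor the SD of walking pain, so size and direction cannot be settled from it. The primary outcome is not affected. A change is worth making because the rule is already fixed, can be corrected cheaply, and is better settled before any data are seen.

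**What to change.** In section 2.8:

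1. State that inability to walk 10 m at T6 is an observed outcome and is exempt from the missing-data rule.
2. Commit to the linear mixed-effects model for pain in place of the open choice with repeated measures ANOVA, so that T24 scores of patients unable to walk at T6 are used.
3. Prespecify a sensitivity analysis of T6 walking pain across all randomized patients, in which those unable to walk take the worst rank and the groups are compared with a rank-based test. Show it beside the walkers-only result and the frequency unable to walk.
4. Record the reason for inability (pain, weakness, other) on the T6 form. This makes specific what the promise to report reasons for missing data already implies.

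The cost is a few sentences, one form field and one extra analysis, with no change to sample size or visits. The downside is that the worst-rank composite mixes motor block or dizziness with pain; the recorded reasons let a reader judge how far that drives the result.

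### Muscle strength is graded 0–5 but compared only as below grade 3, so weakening within grades 3 to 5 cannot show; add an ordinal comparison

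*Protocol article*

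**What the plan says.** Section 2.8 (Study Period, Data Collection, and Analyses) states that "MMT results will be graded from 5 to 0" and defines each level. Just above the cut the definition is "3 = active motion against gravity without resistance". One level higher, at grade 4, the patient can hold against a moderate load but not a full one. One level lower, at grade 2, the patient moves the joint only when gravity is taken away or with slight help. Grade 5 is motion against maximum resistance.

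Section 2.4 (Outcomes) lists one strength outcome: "The frequency of manual muscle test (MMT) < Grade 3 for dorsiflexion and plantarflexion of the ankle and knee extension at" T6, which is six hours after surgery with a window of one hour either side. The list also has a separate functional outcome at T6, the frequency of patients who cannot walk 10 m with crutches.

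On the analysis, section 2.8 says "Differences in frequencies will be analyzed using" chi-squared or Fisher's exact tests, and "An alpha level of 0.05 is used to determine statistical significance". It names no ordinal analysis of the strength grade and gives no reason for the cut at 3.

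The Introduction sums up earlier studies: "Collectively, these findings suggest a favorable analgesic profile for PPB using larger volumes of local anesthetic without compromising motor function". The article gives no expected rate of any strength grade, and section 2.7 (Sample Size) rests on opioid consumption alone.

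**The concern.** The trial compares two volumes of local anesthetic, and the case for testing the larger one is that it may relieve pain better without costing leg strength. Strength is therefore the natural counterweight to the primary outcome. The scale can show partial weakness, but the stated outcome merges full strength, strength against moderate resistance only, and movement against gravity with no resistance at all.

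Two consequences follow. Partial weakening cannot appear in the comparison. And if loss below grade 3 is rare, as the motor-sparing premise suggests, a comparison of two small frequencies is weak even for the severe weakness that it does count. At stake is what the published result can say about the motor side of a volume recommendation.

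**Working it through.** **Inputs.** 60 patients per arm (section 2.7); events are grades 0–2 and non-events grades 3–5 (sections 2.4 and 2.8); alpha 0.05 (section 2.8). The article does not state whether tests are one- or two-sided at analysis; two-sided is assumed here. All strength rates below are assumptions.

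**1. The plan's own figure.** Section 2.7 gives 56 per group for a 15 mg difference, SD 31.8, one-sided alpha 0.05 and power 0.80:

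n = 2(1.645 + 0.842)² × 31.8² / 15² ≈ 2 × 6.18 × 4.494 ≈ 55.6, so 56.

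This reproduces. It concerns opioid consumption and says nothing about power for strength.

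**2. Shift within grades 3–5.** The event indicator is 0 for grades 3, 4 and 5. If every affected patient moves from grade 5 to grade 4 or 3, the proportion below 3 is the same in both arms. This follows from the definition alone and holds at any n.

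**3. How many events are needed.** With equal arms and no events in one of them, the two-sided Fisher p-value for k events in the other is 2 × C(60,k) / C(120,k).

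| Events | p |
|---|---|
| 4 vs 0 | 0.119 |
| 5 vs 0 | 0.057 |
| 6 vs 0 | 0.027 |

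So 6 of 60 (10%) against none is the smallest significant split of this kind. With 0 of 60 events in an arm, the upper limit of the exact two-sided 95% interval is 1 − 0.025^(1/60) = 0.0596, or 6.0%.

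**4. Power for loss below grade 3.** Power is the sum, over all event counts i and j, of Bin(i; 60, p₁) × Bin(j; 60, p₂) wherever Fisher's p ≤ 0.05.

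| Assumed rate, 10 mL vs 20 mL | Power, 60 per arm |
|---|---|
| 1% vs 5% | 5% |
| 2% vs 10% | 28% |
| 5% vs 10% | 9% |
| 5% vs 15% | 33% |
| 5% vs 20% | 63% |
| 10% vs 20% | 25% |
| 10% vs 30% | 73% |

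**5. What an ordinal comparison adds.** Assume 50/30/15/5% with 10 mL for grades 5, 4, 3 and below 3, and a common odds ratio of 2.5 for weakness with 20 mL. The cumulative odds of at least grade 5, 4 and 3 are 1, 4 and 19. Divided by 2.5 they become 0.4, 1.6 and 7.6, giving about 28.6/33.0/26.8/11.6% with 20 mL. In 4,000 simulated trials with 60 per arm, power was:

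- Fisher on below 3: 14%
- Fisher on 3 or lower: 53%
- Mann-Whitney on the grades: 77%

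| Assumed 10 mL rate below 3 | Odds ratio | Below-3 cut | Ordinal |
|---|---|---|---|
| 2% to 10% | 2 to 3 | 1–49% | 50–91% |
| 40% | 2 to 3 | 40–80% | 52–87% |

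The gain is large when severe weakness is uncommon and small when it is common. These simulations assume proportional odds, the setting that favours an ordinal test.

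**The case against.** The best defence is that the cut is a choice and not a mistake. Below grade 3 means that the patient cannot move the joint against gravity unaided, which is a recognisable functional threshold. It is fixed in advance and assessed blind. Any dichotomy misses shifts that stay on one side of it, and low power for a secondary outcome is ordinary in a trial sized on its primary. All of this stands, and it is why the threshold should stay.

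The walking outcome is a second check: weakness bad enough to stop a patient walking with crutches would be counted there. That also stands, but in part only. It too is yes/no, it is done with support, and it does not measure strength in the three movements.

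A reader might go further and infer any of the following, which the article does not support:

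- **Patients at grade 3 or 4 are classed as unimpaired.** The text does not say so. They are non-events for one outcome.
- **The full grades are thrown away.** Nothing says that the distribution will go unreported. The article is condensed and promises a detailed plan with the publication.
- **The test can hardly detect any motor cost.** That needs event rates that are not given. A large severe deficit has reasonable power, and knee extension below grade 3 may not be rare six hours after knee surgery with a femoral triangle block that includes the nerve to vastus medialis.
- **The trial plans to claim motor sparing from a non-significant result.** No such rule is stated. The hypothesis concerns opioid consumption, and the Introduction's remark on motor function summarises earlier studies.

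**Conclusion.** The point holds in limited form. As stated, the only strength outcome cannot register a shift confined to grades 3 to 5. That rests on the article's own definitions and on no assumed rate. Low sensitivity to loss below grade 3 is conditional: power is between 5% and 33% for the listed scenarios with at most 5% of 10 mL patients and at most 15% of 20 mL patients below grade 3, and rises to 73% for 10% versus 30%. These figures assume two-sided testing and all 60 patients per arm analysed. Rare events fit the motor-sparing premise, but the article gives no rates that would settle it.

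This is an available improvement in the use of data already collected. It is not an error in the plan, and it does not touch the primary analysis.

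**What to change.** Change the analysis wording only:

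1. Keep the frequency below grade 3 as the functional threshold, and report it with the risk difference and an exact 95% confidence interval.
2. For ankle dorsiflexion, ankle plantarflexion and knee extension separately, tabulate the 0–5 grade by arm and add an ordinal comparison: Mann-Whitney with tie correction, or proportional odds. Name one of the two in advance.
3. State that a non-significant result for the threshold will be interpreted through its confidence interval and not taken as evidence of no motor effect.

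The grades are already recorded, so there is no data collection cost. The price is three more secondary comparisons, which should be labelled supportive. Section 2.8 already provides for reporting changes to the statistical plan. The change should be made before unblinding.
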